## Abstract

**Background:**

Child and family social workers in the UK work closely with other agencies including schools and the police, and typically they are based in local authority offices. This study will evaluate the effectiveness of placing social workers in schools (SWIS) on the need for social care interventions. SWIS was piloted in three local authorities in 2018–2020, and findings from a feasibility study of the pilots suggests SWIS may operate through three key pathways: (1) by enhancing schools’ response to safeguarding issues, (2) through increased collaboration between social workers, school staff, and parents, and (3) by improving relationships between social workers and young people.

**Methods:**

The study is a two-arm pragmatic cluster randomised controlled trial building on three feasibility studies which found SWIS to be promising. Social workers will work within secondary schools across local authorities in England. 280 mainstream secondary schools will be randomly allocated with a 1:1 ratio to SWIS or a comparison arm, which will be schools that continue as normal, without a social worker. The primary outcome will be the rate of Child Protection (Section 47) enquiries. Secondary outcomes will comprise rate of referrals to children’s social care, rate of Child in Need (Section 17) assessments, days spent in care, and educational attendance and attainment. The study also includes an economic evaluation, and an implementation and process evaluation. Social care outcomes will be measured in July 2022, and educational outcomes will be measured in July 2023. Days in care will be measured at both time points.

**Discussion:**

Findings will explore the effectiveness and cost-effectiveness of SWIS on the need for social care interventions. A final report will be published in January 2024.

**Trial registration:**

The study was registered retrospectively with the International Standard Randomised Controlled Trial Number registry on 13.11.2020 (ISRCTN90922032).

## Introduction

### Background and rationale

This study will evaluate a programme that aims to embed social workers into schools (SWIS) so that they can work more effectively with education colleagues and with children and families. Education and Children’s Social Care (CSC) have an important inter-agency relationship, and both play a vital role in keeping children safe and promoting their wellbeing. Schools have long been among the major sources of referrals to CSC in the UK, contributing the second highest proportion (18%) of all referrals in 2018/19, behind the police (29%) [1]. Yet the two agencies have different roles and priorities, and significant cultural and organisational differences add to the complexity of working effectively together. SWIS was conceived before Covid-19, but the impact of the pandemic is also putting additional pressure on both schools and social workers [2, 3]. Policymakers have been increasingly interested in finding ways to improve how education and CSC work together to respond to safeguarding concerns and protect children, and in this context these efforts are likely to intensify.

SWIS may be a promising approach to doing this. The central idea is that having a social worker linked to and based within a secondary school can have a range of benefits. In particular, to improve the service delivered to children and families, enhance interagency working, reduce risks to children and lead to better outcomes. Building on a recent set of three pilot studies [4], this project is an evaluation of the next stage of development of SWIS: a scaling up trial involving 280 schools in 21 local authorities (LAs) across England, with half of these schools receiving a social worker. Aside from the SWIS pilots, there are several examples of social workers working in schools [5, 6]. However, the scale of the SWIS programme makes this the largest example of the approach.

The three pilot studies have been central to the development of the SWIS study. They took place in Southampton, Lambeth and Stockport in 2018–20. The pilot evaluation generated qualitative and limited quantitative evidence that the intervention was positively received by schools, social care, children and families [4]. A range of benefits were evidenced, including the opportunity for social workers to do more meaningful direct work with children, help a wider range of children and families than they otherwise would, and support schools to work through safeguarding issues. The evaluation also found indications of a reduction in Child in Need and Child Protection assessments carried out. However, the strength of the evidence was limited by the quasi-experimental design, small sample size, low incidence rates of key outcomes, and short follow-up. Taken together, the qualitative and quantitative findings from the pilots prompted the Department for Education to fund this larger trial of SWIS. Delivered through What Works for Children’s Social Care, this scale-up allows us to understand the potential effectiveness of SWIS more robustly.

### Objectives

Study research questions (RQs) relate to (1) impact evaluation, (2) implementation and process evaluation, and (3) economic evaluation.

#### Impact evaluation

The primary research question is: What is the impact of SWIS in reducing rates of Section 47 enquiries (across 2 academic years, starting on 2nd September 2020 and measured 23 months later), compared to usual practice? (***RQ1***) Secondary research questions are: What is the impact of SWIS on:

rates of referral to CSC and Section 17 assessments? (across 2 academic years, starting on 2nd September 2020 and measured 23 months later) (***RQ2***)the number of days children spend in care? (across 2 academic years, starting on 2nd September 2020 and measured 23 and 35 months later) (***RQ3***)educational attendance (recorded termly across 2 academic years, starting on 2^nd^ September 2020) (***RQ4***) and attainment (recorded June 2021 and 2022)? (***RQ5***)

#### Implementation and process evaluation

Research questions in this part of the study are: Is SWIS implemented as intended? (***RQ6***), what evidence is there for the mechanisms of change identified in the logic model? (***RQ7***), and how does SWIS impact the wider social care system? (***RQ8***).

#### Economic evaluation

The research question in this part of the study is: What is the additional cost associated with SWIS and is it justified by improvements in student outcomes? (***RQ9***).

The full study protocol is available at https://whatworks-csc.org.uk/research-project/social-workers-in-school-scale-up/.

## Materials and methods

### Trial design

The study is a pragmatic cluster randomised controlled trial with two arms (one intervention and one control group) and mainstream secondary schools as the unit of randomisation.

### Study setting

The study will be conducted in mainstream secondary schools in England, across 21 LA areas.

### Eligibility criteria

Mainstream secondary schools are places of education for children aged between 11 and 18 (Years 7 to 13). They are funded by the Government and provide a free education for children, though a number of models exist, such as academies, free schools, and faith schools. All children attending the schools are eligible for the trial. Schools may opt-out of participation in the Implementation and Process Evaluation (IPE) while remaining in the trial.

### Who will take informed consent?

Informed consent will be obtained from all individuals who take part in aspects of the IPE (e.g. surveys and interviews). Researchers will take consent, and receive signed consent forms and/ or audio recorded verbal consent from participants.

### Intervention and control conditions

The intervention physically locates social workers within schools with the aim to build better working relationships with school staff, students and families. Rather than working with students and families from a LA office base, and liaising with and providing advice to education professionals remotely, the social worker is embedded in the school. S1 Appendix shows a logic model that describes three hypothesized mechanisms of impact:

Enhanced school response to safeguarding issuesIncreased collaboration between social worker and school staff, and parentsImproved relationships between social worker and young people

Pathway A is based around regular, good quality, communication between the social worker and school staff. The advice and support given to school staff is hypothesized to increase staff confidence in safeguarding issues and improve the quality of school referrals. Pathway B is about working directly with families and improving relationships between social workers and parents. Pathway C is about working with children and young people directly. Frequent interactions with the social worker enable the young person to trust the social worker and to feel understood and supported. This is theorised to lead to improved school attendance and participation, better management of a young person’s risks and improved outcomes. In all three pathways, improved child and family outcomes are theorized to lead to a reduction of the number of children in care.

Following the pilot evaluations, an intervention manual has been developed (WWCSC, 2020 –available on request from [contact]). This distils the key messages from the pilots into a practical format designed to assist the 21 LAs in delivering SWIS. Its stated aim is to provide “a framework to refine the SWIS Scale-up programme and encourage more consistent and effective integration of social workers into schools”, although the need for flexibility is acknowledged. The manual offers a number of recommendations for implementers. Among them, the following relate to programme delivery:

Social workers should be embedded within secondary schools, but can work with feeder primaries.Social workers linked to schools should be experienced (being in practice for at least 2 years).The focus should be on statutory social work with additional opportunities for “preventative” aspects, which could involve “advising staff, families and young people” and working with children who are not at the threshold for formal involvement.Caseloads should be managed by the SWIS team manager and be in line with LA averages, and where possible the carry-over of existing caseloads prior to the launch should be minimal. To avoid disrupting existing relationships SWIS workers are expected to take on new cases.Social workers should be embedded in schools as far as possible, with their own office space in the school and opportunities to integrate.Face to face contact should be the basis for the intervention, in order to build strong relationships with school staff, children and families.

The control group will receive service as usual. Children who are deemed by school staff to require the involvement of CSC will be referred to the LA, usually via telephone call or email to a Multi-Agency Safeguarding Hub arrangement or a referral and assessment team. Children judged by CSC to meet the threshold for involvement will be allocated a social worker as usual, but social workers will not be based in the school. This was chosen as the comparator because it is the status quo that the intervention can be distinguished from, and the system that SWIS needs to perform better than if it is to be considered worthwhile. Children who are deemed to require the involvement of CSC will continue to be eligible for this across all schools, including the control group. LAs will make case by case judgements about the best interests of children who were receiving a service prior to the trial. For example, a child on an existing child protection plan may retain their previously allocated social worker to avoid disruption, rather than transferring to the SWIS worker.

### Strategies to improve adherence to interventions

We anticipate good adherence to the intervention, as the funding for the trial intervention (i.e. the social worker) is provided to participating LAs and schools on the basis of compliance with the intervention guide supplied by the funder, and LAs have committed to delivering SWIS as described. All schools also confirmed their commitment at the outset. However, the adverse circumstances of Covid-19 may mean that some sites need to adapt SWIS, for example to accommodate social distancing or increased remote working. The IPE is designed to capture such adaptation and secondary analyses will explore the impact of varied levels of adherence.

### Outcomes

#### Primary outcome

*Child protection (Section 47) enquiries*. Child protection (s.47) enquiries are investigations CSC carry out when they have “reasonable cause to suspect that a child who lives, or is found, in their area is suffering, or is likely to suffer, significant harm” (Children Act, 1989). This is a key point in the work of CSC; an enquiry would normally involve an assessment of the child’s needs and the ability of family members or carers to meet them. Social workers would normally interview family members, children (if they are old enough), and use information from other agencies such as schools and health. This data will be collected from LA CSC departments, based on a data sharing agreement between each LA and the research team.

Child protection (s.47) enquiry starts will be recorded as a binary (no enquiry/ enquiry started) variable. If the s.47 start date lies between and including the start date of the academic year (2nd September, 2020), and 31st July 2022, it will be coded 1, otherwise it will be coded 0. Enquiries will be recorded at the individual-level, then aggregated at the school-level and shared with the research team. This aggregated count variable will be our outcome measure.

#### Secondary outcomes

The following CSC data will be collected from LA CSC departments, based on a data sharing agreement between each LA and the research team.

*Referrals to CSC*. Referrals are made to CSC when someone thinks a child is at risk, and schools are typically the second highest agency referrer (after the police) (Further details can be found in the version of this protocol published by the funder: [name] et al., 2020. Referral dates will be recorded and referrals will be recorded as a binary (no referral/ referral) variable. If a referral date lies between and including the start date of the academic year (2^nd^ September, 2020), and 31st July 2022, it will be coded 1, otherwise it will be coded 0. This will be recorded at the individual-level, then aggregated at the school-level and shared with the research team. This aggregated count variable will be the outcome measure.*Child in Need (s*.*17) assessments*. A Child in Need assessment aims to identify the needs of a child or children within a family, and ascertain what support the family needs to meet them. Start dates for assessments will be recorded and assessments will be recorded as a binary (no assessment/ assessment) variable. If the start date for assessment lies between and including the start date of the academic year (2nd September, 2020), and 31st July 2022, it will be coded 1, otherwise it will be coded 0. These will be recorded at the individual-level, then aggregated at the school-level and shared with the research team. This aggregated count variable will be the outcome measure.*Days in care*. We will record the total number of days children spend in care for two time periods, 23 months and 35 months, from (and inclusive of) the start date of the academic year (2^nd^ September, 2020). We will create two variables, one that counts the number of days spent in care between and including this date and 31st July 2022, and the other that counts the number of days spent in care between and including 2^nd^ September 2020 and 31st July 2023. The inclusion of days in care at the 35 month timescale (as well as measuring it along with other CSC outcomes at 23 months) is because impact on this outcome is more likely to become clear with a longer follow-up. This will be recorded at the individual level, then aggregated at the school-level and shared with the research team. This aggregated count variable will be the outcome measure.

The following data will be collected from the Department for Education’s National Pupil Database (NPD), and will be made available to the research team in anonymised form at an individual level (identifiers will be stripped from the dataset) [7]. One application will be made to the NPD in early 2023 to request access to the following datasets:

*Educational attendance*: *Unauthorised absences (%)*. This is the percentage of sessions (half days) that children are absent without being authorised, out of the number of sessions possible. The data are available via the NPD absence dataset. For the 2020/21 academic year, these data will be released by the NPD in March 2022, and for the 2021/22 year they will be released from October 2022 (unamended) to March 2023 (final); access will be requested for the final datasets for both years in April 2023. This variable will be defined by the number of sessions missed due to unauthorised absence per term (Autumn, Spring, Summer) out of the number of sessions possible per term.*Educational attainment at Key stage 4*. Key stage 4 (General Certificate of Secondary Education: GCSE) results are the key educational outcome measure for secondary school pupils. Educational attainment at Key Stage 4 (KS4) for the 2020/21 academic year will be released in April 2022, and in April 2023 for the 2021/22 academic year; access will also be requested for both years in April 2023. The following outcomes will be reported for all pupils completing GCSE exams in 2021 and 2022 or subject to equivalent grading exercise (a subset of those pupils included in the trial):
○ Attainment 8 –a measure of a pupil’s average grade across eight agreed GCSE subjects○ English Baccalaureate Average Point Score–an agreed set of GCSE subjects (English language and literature, maths, the sciences, geography or history and a language)○ % English and maths, grade 5 and above. This will be a binary variable coded 1 if the pupil achieved a level 5 or higher in both English and maths, and coded 0 otherwise

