### Statistical methods

#### Statistical methods for primary and secondary outcomes

All primary analyses will be ‘intention to treat’ i.e. schools will be analysed in the groups to which they were randomised, regardless of adherence to the intervention. Missing outcome data will not be replaced. For the primary outcome analysis, a quasi-Poisson regression model will be fitted with fixed effects for LAs and cluster robust standard errors reflecting the clustering structure (schools within LAs) to compare rates of s.47 enquiries at 23 months by arm, using the number of students per school as the exposure scaling variable, and s.47 enquiries for 2018/19 (baseline) and % eligible for FSM as fixed-effect covariates. Using a quasi-likelihood model accounts for possible over- or underdispersion i.e. variance in the data that is higher or lower than expected under the standard Poisson model. Allocation will be included in the model as a fixed effect, and the intervention effect (model coefficients transformed into rate ratios) will be presented as point estimate with two-sided 95% confidence interval (CI) and p-value. If the estimated rate is lower in the SWIS arm than in the comparator arm and the 95% CI around the estimated rate ratio excludes the null effect (rate ratio = 1), effectiveness of SWIS at the 5% level will be concluded.

Secondary outcomes will be analysed in a similar way as the primary outcome, by fitting regression models with cluster robust standard errors depending on the type of outcome: quasi-Poisson for rates (referrals to CSC, s.17 assessments) and linear for continuous variables (days in care, educational attendance and attainment). For the school-level variables (referrals to CSC, s.17 assessments, days in care) we will include the same fixed-effect covariates in the model as for the primary outcome (allocation, LA, baseline outcome from 2018/19, % eligible for FSM) and also use the number of students per school as the exposure scaling variable. For the student-level variables (educational attendance and attainment) we will additionally include gender and ethnicity as covariates, and the baseline outcomes used will be 2018/19 attendance (for attendance) and KS4 results (for attainment). The p-values generated from the secondary outcome analyses will be adjusted for multiplicity using Hochberg’s step-up procedure.

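### Days in care includes care spells already open on 2 September 2020, and the planned model has no covariate for how many children were in care on that day, which costs precision

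*Protocol article*

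**What the plan says.** Under Secondary outcomes the article says "We will record the total number of days children spend in care for two time periods, 23 months and 35 months", both running from 2 September 2020. The first variable is "one that counts the number of days spent in care between and including this date and 31st July 2022"; the second runs to 31 July 2023. Individual days are summed to a school total. Nothing restricts the count to spells that began in the window. The longer window was added because an effect on this outcome is expected to show more clearly with time.

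The other social care outcomes are dated events. An s.47 enquiry, for example, is coded 1 only "If the s.47 start date lies between and including the start date of the academic year (2nd September, 2020") and the end of July 2022.

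Under Statistical methods for primary and secondary outcomes, days in care is analysed by a linear model with these covariates: "allocation, LA, baseline outcome from 2018/19, % eligible for FSM".

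On who receives the intervention, Intervention and control conditions says: "To avoid disrupting existing relationships SWIS workers are expected to take on new cases". It adds that "where possible the carry-over of existing caseloads prior to the launch should be minimal", and that "LAs will make case by case judgements about the best interests of children who were receiving a service prior to the trial". Its example is that "a child on an existing child protection plan may retain their previously allocated social worker".

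**The concern.** A child in care throughout adds 698 days to the school's 23-month total and 1,063 to its 35-month total, even if the spell began long before launch. SWIS workers are mainly meant to pick up new cases, so any effect through fewer entries to care acts only on the remaining days. The days from open spells dilute that effect. They also vary between schools, because the number in care on the opening day varies by chance and by school.

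A baseline covariate could absorb much of this variation, but the planned one is dated. Children in care in 2018/19 may have left care by September 2020, and others will have entered. RQ3 is a named research question tested at two time points. An imprecise null result there would leave unclear whether SWIS had no effect or the measure was too noisy to show one.

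**Working it through.** **Inputs from the article.** 140 schools per arm and 925 pupils per school (Sample size); window dates (Secondary outcomes); covariates (Statistical methods). The article states no power, spell length, entry rate or number in care for this outcome, so there is no figure to reproduce.

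**Window lengths.** 2 September 2020 to 31 July 2022 inclusive is 698 days (22.9 months); to 31 July 2023 it is 1,063 days (34.9 months). If the 2018/19 year is taken to end on 31 July 2019, the gap to 2 September 2020 is about 13 months.

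**Share of days from open spells.** Assume a steady state with exponential spells of mean m months and N children in care at any time. Open spells contribute N·m(1 − exp(−T/m)) over a window of T months, and the total is N·T. The share is therefore s = m(1 − exp(−T/m))/T. For m = 24 and T = 22.9: 24 × (1 − exp(−0.955))/22.9 = 24 × 0.615/22.9 ≈ 0.64.

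| Assumed mean spell | 23 months | 35 months |
|---|---|---|
| 6 months | 26% | 17% |
| 1 year | 45% | 32% |
| 2 years | 64% | 53% |
| 3 years | 74% | 64% |

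The result depends on the distribution as well as the mean: fixed-length spells of 6 months, 1, 2 and 3 years give 13%, 26%, 52% and 68% at 23 months.

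**Dilution.** If open spells are unaffected, a 20% cut in new entries shows as (1 − s) × 20% of total days. At 23 months this is 0.55 × 20 = 11%, 0.36 × 20 ≈ 7% and 0.26 × 20 ≈ 5% for mean spells of 1, 2 and 3 years.

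**Power at 23 months, by simulation.** Assumptions: 280 schools of 925 pupils; 6 per 1000 in care (925 × 0.006 ≈ 5.6 children per school); between-school coefficient of variation 0.3; exponential spells; linear model with allocation and 2018/19 days. The 2018/19 days come from the same continuing process, so long spells carry over into the window. Local authority effects and free school meals were not simulated. Each cell gives power for mean spells of 1/2/3 years.

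| Analysis | 20% fewer entries | Stays 20% shorter |
|---|---|---|
| Total days, planned model | 70/36/23% | 84/45/34% |
| Total days plus number in care on 2 September 2020 | 93/66/49% | 97/80/63% |
| Days from spells starting in the window | 97/85/72% | 52/14/10% |

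Independent runs differ by a few percentage points; for the first cell they gave 70–72, 34–36 and 23–26%. With a mean spell of 6 months, power for fewer entries is already near its ceiling under all three analyses, so the covariate gains little there.

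**The case against.** The strongest reply is that total days is the right outcome. RQ3 asks about days children spend in care, and the logic model ends in fewer children in care. That number falls through fewer entries or earlier exits, and total days captures both. Referrals, s.17 assessments and s.47 enquiries are events, so a start-date rule suits them; care is a duration, and a different rule is no inconsistency. This stands. It is a reason not to make days from new spells the tested outcome, which would lose most of its power if SWIS mainly shortened stays.

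A reader might also infer that half to three quarters of the total comes from children SWIS is not meant to take on. The article does not support this. That share requires an assumed exponential mean spell of about 14 to 38 months, and no spell length is given. Carry-over is to be minimal only where possible, local authorities judge case by case, and the example concerns a child protection plan, not a child in care.

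Third, the plan has safeguards. The 2018/19 baseline was chosen deliberately as the last year unaffected by Covid-19, and with long spells it shares some spells with the window. The 35-month window lowers the open-spell share, and planned-model power for fewer entries rises there to about 92/62/41%. Monthly data are also collected. These points reduce the loss but do not remove it: none of them puts the number in care on the opening day into the model.

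**Conclusion.** The point holds as a matter of precision. The outcome mixes open and new spells, and the only outcome baseline predates the window by about 13 months. A reader might take this for bias, but open spells predate the window and randomisation within local authorities balances them in expectation, so the estimated effect on total days remains valid.

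The size is conditional. The open-spell share and the power loss both grow with spell length, and spell length, prevalence and between-school variation are all assumptions here. For mean spells of 1 to 3 years, the missing covariate costs roughly 23 to 30 percentage points of 23-month power if SWIS reduces entries (93 − 70 = 23, 66 − 36 = 30, 49 − 23 = 26). If it shortens stays, the cost is 13 to 35 points (97 − 84 = 13, 80 − 45 = 35, 63 − 34 = 29). For spells of about 6 months the loss is small. This is a worthwhile improvement to a secondary analysis, not a flaw in the trial's main conclusion.

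**What to change.** Keep total days in care as the tested outcome at both time points. Add each school's number of children in care on 2 September 2020 as a covariate alongside the 2018/19 value. This leaves the estimand unchanged and raised power under both mechanisms for mean spells of 1 to 3 years.

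Report days from spells starting on or after 2 September 2020 as a supportive outcome only, to help separate an effect on entries from one on length of stay.

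The cost is one or two extra aggregate fields in the local authority proforma and a sentence in the analysis plan. Local authorities already record days in care per child before aggregating, so the opening-day count should be within reach. The supportive outcome also needs spell start dates, which the article does not mention for care, so availability should be confirmed with the data leads. Both fields should be requested with the extracts, because school totals alone cannot supply them later.

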#### Education data

Education attainment and attendance data will be accessed via the NPD. LAs will confirm the school identifier to the Cardiff team (Unique Reference Number, URN) to enable NPD to identify pupils in those schools. Education data for those pupils will be made available to the study team via their Secure Research Service–a remote access data safe haven (hosted by the Office for National Statistics) as per their data sharing processes [13].

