#### Other secondary analyses

A secondary analysis will use per-term (or per-month, if available) outcome data and include term (or month) as an additional covariate in the model to explore potential implementation effects and/or seasonality. Another secondary analysis will assess the hypothesised mediators of change outlined in logic model (S1 Appendix) at the 23-month follow-up by fitting an interaction term between allocation and category of implementation fidelity (a Gold, Silver, Bronze categorisation will be developed based on a re-analysis of pilot data and other insights from the IPE). Any other subgroup analyses (e.g. by age group) will be agreed with service user input. The p-values generated from these secondary and subgroup analyses will also be adjusted for multiplicity using Hochberg’s step-up procedure. We will fit a two-level mixed-effects model with random LA effects as an additional robustness analysis.

Missing outcome data will not be replaced in the primary analysis, but we will perform null imputation for missing covariates, where we will replace missing values with 0, and create a dummy indicator for the covariate coded 1 if the value was missing, and 0 otherwise, and include the dummy in the regression. If more than 5% of outcome data are missing, we will consider repeating the primary analysis after multiple imputation. To assess the impact of non-compliance (if present), we will exclude intervention arm schools that did not adopt the intervention at all and then repeat the primary analysis, and we will also perform a complier average causal effect (CACE) analysis. Statistical code and anonymised data can be provided upon reasonable request, in line with Centre for Trials Research policy.

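### The Key Stage 4 attainment set depends on completing or being graded at GCSE, which is settled after randomisation and which SWIS could influence, so the RQ5 comparison could be biased

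*Protocol article*

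**What the plan says.** The protocol article, Secondary outcomes, sets the population for Attainment 8, the English Baccalaureate Average Point Score and the English and maths measure: "The following outcomes will be reported for all pupils completing GCSE exams in 2021 and 2022 or subject to equivalent grading exercise". It calls this group "a subset of those pupils included in the trial". The English and maths measure is "coded 1 if the pupil achieved a level 5 or higher in both English and maths, and coded 0 otherwise".

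Other sections that bear on the point:

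- Eligibility criteria: "All children attending the schools are eligible for the trial".
- Intervention and control conditions, on the pathway of direct work with young people: "This is theorised to lead to improved school attendance and participation".
- Education data: local authorities confirm each school's reference number "to enable NPD to identify pupils in those schools". No roll date is given.
- Statistical methods for primary and secondary outcomes: intention to treat means that "schools will be analysed in the groups to which they were randomised, regardless of adherence to the intervention". The student-level models add gender and ethnicity as covariates.
- Other secondary analyses: "Missing outcome data will not be replaced in the primary analysis, but we will perform null imputation for missing covariates". Multiple imputation is only considered, and only for the primary analysis.

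**The concern.** Randomisation makes the pupils of the two arms comparable at the start. It does not make those who later reach a GCSE grade comparable if reaching one depends partly on the arm. Suppose SWIS keeps some pupils engaged who would otherwise have left or gone ungraded, and these pupils score below average. They then enter the SWIS mean, while their counterparts in control schools are absent from the control mean. The SWIS arm can look worse although no pupil did worse. If SWIS instead led to more pupils moving away, the distortion would run the other way.

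What is at stake is the answer to RQ5, which rests on all three attainment measures. More schools or pupils would not remove a bias of this kind.

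**Working it through.** The protocol gives no sample-size, completion or effect figure for attainment, so there is no stated figure to reproduce. The first three steps compare the text; the fourth illustrates size on assumed inputs.

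**1. When is membership settled?** The outcome window opens on 2 September 2020, and Objectives records attainment in June 2021 and June 2022. Membership is therefore settled about 9 and 21 months after the window opens.

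**2. Could SWIS influence it?** Intervention and control conditions names attendance and participation. It does not name GCSE entry, GCSE completion or staying on roll. The step from participation to being entered and graded is a short inference, but it is an inference.

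**3. Does anything in the text protect the comparison?**
- Intention to treat fixes the arm of each school, not which pupils are counted.
- Identification by school number without a roll date does not secure pupils who left.
- Missing outcomes are not replaced.
- Gender and ethnicity do not adjust for selective completion.
- The zero coding of the binary measure, as worded, sits inside the reported set. Whether it reaches pupils with no result is not stated.

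**4. How large could it be?** All inputs here are assumptions:
- p, completion in control schools: 90 to 98%.
- d, extra completion under SWIS: 0.5 to 2 percentage points.
- D, gap between the extra completers and the rest: 0.5 to 1.5 SD.
- No effect of SWIS on the other pupils.

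Set the other completers' mean to 0 and the SD to 1. The control mean is 0. The SWIS mean is (p × 0 + d × (−D)) / (p + d), so

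shift = −dD / (p + d).

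| p | d | D | Calculation | Shift (SD) |
|---|---|---|---|---|
| 0.98 | 0.005 | 0.5 | −0.0025 / 0.985 | −0.0025 |
| 0.95 | 0.01 | 1.0 | −0.010 / 0.96 | −0.0104 |
| 0.90 | 0.02 | 1.5 | −0.030 / 0.92 | −0.0326 |

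The first and last rows are the extremes of the range. A gain of g = dD / p among the other pupils would cancel the shift: 0.0025 / 0.98 = 0.0026 SD at the low end and 0.030 / 0.90 = 0.0333 SD at the high end.

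For the English and maths measure, assume also 50% success among the other completers and q = 0 to 20% among the extra completers:

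shift = d(q − 0.5) / (p + d).

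- Smallest: 0.005 × (−0.3) / 0.985 = −0.15 percentage points.
- Largest: 0.02 × (−0.5) / 0.92 = −1.09 percentage points.

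If the whole GCSE year group is counted and pupils without a result are coded 0, the difference becomes d × q, which is 0 to 0.02 × 0.2 = +0.4 percentage points. On the same inputs, the completers-only contrast shows a fall where the whole-cohort contrast shows no change or a small gain.

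**The case against.** The strongest reply is that the sentence may do no more than name the year groups that have Key Stage 4 data. The trial covers schools with Years 7 to 13, so most of the restriction to a subset is simply the two GCSE cohorts, and SWIS cannot change a pupil's year group. That stands for most of the subset. It does not dispose of the point, because the wording also makes completion or grading a condition.

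A reader might infer that anyone who does not sit an exam is lost. The text does not support that. Pupils graded by an equivalent exercise are included, and the Discussion says teacher-assessed grades replace exams in 2021. This narrows the problem for one cohort, although the text does not say what happens to a pupil who has left the roll.

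A reader might also infer that SWIS is designed to change GCSE completion, or that the plan would necessarily lower the SWIS arm's score. Neither is in the documents. The first goes beyond the attendance and participation that are named. The second needs an arm difference in completion, below-average extra completers and no offsetting gain elsewhere, none of which is shown.

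The handling of leavers can fairly be left to the full protocol or the analysis plan, and silence on it is not the finding. The finding is the population rule that the article does state.

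Finally, scoring every pupil without a result as 0 may treat pupils who moved or could not be linked as failures. That is a good reason to keep zero scores for the two point-score measures out of the main analysis.

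**Conclusion.** The point holds in a limited form. The stated attainment population depends on a status settled after randomisation that SWIS could influence, and nothing in the text protects the pupil-level comparison. Bias in RQ5 is therefore possible, and its likelier direction is against SWIS.

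The size is probably small: about 0.03 SD or less, or roughly 0.15 to 1.1 percentage points on the binary measure. Both ranges rest wholly on assumed completion rates, gaps and pass rates. The protocol states no target effect for attainment against which to judge them. Attainment is a secondary outcome, and the conclusion on Section 47 enquiries does not depend on it. The change is worth making because it is cheap and because the bias, if present, would be hard to recognise afterwards.

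**What to change.** - Define the attainment population as Year 10 and Year 11 pupils on roll at a trial school at the start of autumn term 2020. Analyse each by the school held at that date, using Key Stage 4 results wherever the NPD records them.
- Word the NPD request accordingly, by autumn 2020 roll.
- On the English and maths measure, code as 0 every pupil in this population without grade 5 or higher in both subjects.
- Report the proportion without Key Stage 4 results by arm.
- For Attainment 8 and the English Baccalaureate score, add a sensitivity analysis that scores missing results as 0.
- Keep the completers-only result as supplementary.

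The cost is a change of outcome wording and of the data request. The education data are already individual-level, and the single NPD application is planned for early 2023. There are two downsides. Pupils who join after the roll date leave the main attainment analysis. Some leavers may not link to a result, so the fix reduces the selection without removing all of it; the report of missing results by arm and the zero-score sensitivity analysis show how much remains.
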